# A randomised controlled trial of an implementation strategy delivered at scale to increase outdoor free play opportunities in early childhood education and care (ECEC) services: a study protocol for the get outside get active (GOGA) trial

**DOI:** 10.1186/s12889-022-12883-w

**Published:** 2022-03-29

**Keywords:** Outdoor play, Free play, Physical activity, Indoor-outdoor, Early childhood education and care, Implementation trial, Randomised controlled trial

## Abstract

**Background:**

Increased outdoor play time in young children is associated with many health and developmental benefits. This study aims to evaluate the impact of a multi-strategy implementation strategy delivered at scale, to increase opportunities for outdoor free play in Early Childhood Education and Care (ECEC) services.

**Methods:**

The study will employ a parallel-group randomised controlled trial design. One hundred ECEC services in the Hunter New England region of New South Wales, Australia, will be recruited and randomised to receive either a 6-month implementation strategy or usual care. The trial will seek to increase the implementation of an indoor-outdoor routine (whereby children are allowed to move freely between indoor and outdoor spaces during periods of free play), to increase their opportunity to engage in outdoor free play. Development of the strategy was informed by the Behaviour Change Wheel to address determinants identified in the Theoretical Domains Framework. ECEC services allocated to the control group will receive ‘usual’ implementation support delivered as part of state-wide obesity prevention programs. The primary trial outcome is the mean minutes/day (calculated across 5 consecutive days) of outdoor free play opportunities provided in ECEC services measured at baseline, 6-months (primary end point) and 18-months post baseline. Analyses will be performed using an intention-to-treat approach with ECEC services as the unit of analysis, using a linear mixed effects regression model to assess between-group differences. A sensitivity analysis will be undertaken, adjusting for service characteristics that appear imbalanced between groups at baseline, and a subgroup analysis examining potential intervention effect among services with the lowest baseline outdoor free play opportunities.

**Discussion:**

Identifying effective strategies to support the implementation of indoor-outdoor routines in the ECEC setting at scale is essential to improve child population health.

**Trial registration:**

Australian New Zealand Clinical Trials Registry (ACTRN12621000987864). Prospectively registered 27th July 2021, ANZCTR - Registration.

## Background

Outdoor play is recognised as essential for healthy child growth and development [1]. Systematic review evidence suggests that increased outdoor play time in children aged 3–12 years is associated with increased moderate-to-vigorous intensity physical activity (MVPA) and cardiorespiratory fitness, as well as accruing other social, emotional, and cognitive benefits [2, 3]. Building on the time-use epidemiology pertaining to 24-h movement behaviours recommended by international guidelines [4, 5], transitioning some indoor only play time to outdoor play time can provide children with additional opportunity to accumulate the benefits of outdoor play. Despite this, national surveys conducted in the United States (US) [6], Canada and Australia suggest that the amount of outdoor play that young children participate in has declined over the last 20 years [7]. As such, leading international organisations including the US Centres for Disease Control Obesity Centre [8], and the United Kingdom’s (UK) Play Safe Forum [9] have recommended increasing opportunities for child self-directed (‘free’) play outdoors in all settings including home, schools, early childhood education and care (ECEC) services and the community [1].

In many countries, ECEC services provide access to the majority of young children aged 0–5 years for a significant proportion of their waking hours [10]. ECEC services therefore have a crucial role in ensuring sufficient opportunities for outdoor play for young children. Almost all ECEC services have the infrastructure and spaces to create environments to support physically active outdoor play [11]. Furthermore, accreditation processes and best-practice guidelines for the ECEC sector recommend that services implement several evidence-based practices supportive of outdoor free play. This includes creating conducive outdoor environments and allowing children to move freely between indoor and outdoor spaces (also known as indoor-outdoor play) [12]. A systematic review of observational ECEC-based studies reported that young children have higher total physical activity outdoors compared to indoors while in care [13]. Increasing outdoor free play opportunities by one hour increased child total physical activity by 25 min, of which 10.7 min was MVPA [13]. Such findings are supported by a recent randomised controlled trial (RCT) conducted in 10 ECEC services, which found that increasing frequency and/or duration of outdoor free play in ECEC services improved child MVPA [14].

Despite best practice guidelines and evidence supporting the need to increase outdoor free play opportunities in ECEC services [1, 15, 16], the amount of time for child-directed outdoor free play remains low [17]. Recommendations for the ECEC sector specify that children should spend between 12 and 20% of the ECEC day engaged in outdoor free play [18, 19]. Observational studies in the US, however, have found that children in care spend an average of 33 min in outdoor free play, representing just 8% of the ECEC day [15]. A national survey of 203 Australian ECEC services indicated that approximately 60% were currently implementing routines including indoor-outdoor play to increase time spent outdoors [20]. Although the majority of ECEC managers indicate being supportive of outdoor free play and implementing indoor-outdoor routines, they also report the need for assistance with planning appropriate staffing and practical strategies to orientate the layout of their service to facilitate transitions outside [20].

Maximising the potential benefits of outdoor free play on child health requires strategies to support the implementation of routines that are conducive to outdoor play at scale. Scaling up has been defined as “a deliberate process of taking health interventions that have been proven effective on a small scale and expanding their reach to larger number of users in real world settings while maintaining efficacy” [21, 22]. The World Health Organization has identified scaling up of programs as crucial to ensuring benefits at a population level [23]. Despite this, less than 3% of physical activity interventions are successfully implemented at scale and very little is known about how to scale-up physical activity programs [24, 25]. In ECEC services, a recent Cochrane review [26], found only two controlled trials that assessed the impact of strategies to increase the implementation of physical activity (PA) programs at scale (defined as > 50 ECEC services in the intervention arm) [27, 28] providing little information about how to support implementation of evidence-based physical activity programs in ECEC services at scale.

This protocol (version 1) describes the methods for an RCT that aims to assess the impact of a multi-strategy implementation strategy, delivered at scale, to increase opportunities for outdoor free play in ECEC services.

## Methods

The study methods will be reported in accordance with the CONSORT reporting standards for RCTs, [29] the Standards for Reporting Implementation Studies (StaRI) statement [30], and is consistent with best practice guidance for undertaking implementation trials [31]. The trial was prospectively registered with the Australian New Zealand Clinical Trials Registry (ACTRN12621000987864). Ethics approval has been provided by Hunter New England (HNE) Human Research Ethics Committee (HREC) (reference no 2019/ETH12353), Swinburne University of Technology HREC (reference no 20215523–5944) and University of Newcastle HREC (reference no H-2008-0343). This protocol has also been reported according to the Standard Protocol Items: Recommendations for Interventional Trials (SPIRT) [32].

### Study design and setting

The study will employ a two-arm parallel-group RCT design. One hundred ECEC services in the HNE region of New South Wales (NSW) Australia will be recruited and randomised to receive either a 6-month implementation strategy or usual care. The trial will assess between-group differences in the mean minutes children are provided with the opportunity for outdoor free play per week, with data collected at baseline (approximately November 2021–February 2022), and immediately following the delivery of the 6 month implementation strategy (primary time point, T_5_). Data will also be collected approximately 12-months following completion of the implementation strategy to determine the longer-term impact of the intervention (18-months follow up, T_6_) (Fig. 1).

**Fig. 1 Fig1:**
[figure not shown]
SPIRT Figure

### Participants and recruitment

#### Sampling frame

A list of all centre-based ECEC services (i.e. long day care and preschool services) located in the HNE Local Health District (LHD) of NSW, Australia (*n* = 440) will be accessed via NSW Centre for Population Health (CPH) records [33] and will serve as the study sampling frame. Within NSW, long day care services provide centre-based care for children from 6 weeks to under 6 years of age for 8 or more hours per day. Preschools typically enrol children between 3 and 6 years of age and provide care for 6 to 8 h per day. The HNELHD area encompasses major metropolitan centres and inner regional communities, with 14% of the population located in remote communities [34].

#### Eligibility

To be eligible to participate, ECEC services must report having at least one session of indoor only free play across five consecutive days, where the opportunity for outdoor free play is not made available to children. Services will be excluded if they are participating in any other trial related to improving physical activity practices, cater exclusively for children with special needs, are an occasional care or family day care service, or are a Department of Education community run service (as such services are not covered within the existing ethics arrangement and consists of less than 10% of services in the HNELHD region).

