### Implementation strategy

#### Theoretical frameworks

The Get Outside Get Active (GOGA) program is an implementation strategy designed to increase the delivery of the evidence-based practice described above. Primarily, services are supported to modify their play routines to convert any indoor only free play routine to also incorporate outdoor play.

The development of the multi-strategy implementation strategy was informed by the Behaviour Change Wheel (BCW) [36] and Theoretical Domains Framework (TDF) [37]. The TDF summarises 33 theories and 128 constructs which may explain implementation behaviour, into 14 domains underpinned by psychological theory. This framework was used to enable comprehensive barriers assessment to inform intervention development [38]. Barriers to service provision of outdoor free play opportunities were first identified via: i) a systematic review of barriers and facilitators to the implementation of physical activity policies in ECEC [39]; b) quantitative survey with ECEC services to assess key barriers and enablers to providing more outdoor free play opportunities [20]; and c) consultation with Service Managers and Educators from five ECEC services about the key barriers to implementation. The barriers identified from this process are described in Table 1. The capability, opportunity and motivation model of behaviour (COM-B) of the BCW was then used to distil the TDF into these three key domains to enable selection of intervention functions [38].

**Table 1 Tab1:** Logic model outlining GOGA development

**Proposed mechanisms of action**			**Content**	
Target behaviour: Amending all indoor only free play time to allow children the opportunity to access outdoor areas				
**Barriers reported by ECEC services**	COM-B and (TDF)	Intervention function	Behaviour Change Techniques (BCTs) applied	Implementation strategy (modality)
Staff lack of awareness of the benefits of outdoor play and implementing indoor-outdoor routines.	Capability – psychological (Knowledge).	Environmental restructuring Education	Information about health consequences. Information about social and environmental consequences. Instruction on how to perform the behaviour.	Develop educational resources (email and hard copies via mail).

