### Analysis and sample size

Analyses will be performed using an intention to treat approach, with ECEC services as the unit of analysis. Separate analyses will be performed at each follow-up time point (6 and 18 months). Intervention effects on the primary trial outcome (at each follow-up time point) will be assessed using a linear mixed effects regression model, which will include fixed effects for the treatment group (intervention vs control), the baseline value of the outcome and variables that are prognostic of the outcome (service size and geographical region). Multiple imputations will be performed for ECEC services not providing follow up data in accordance with the recommendation by White and colleagues [64] and presented as the primary analysis. Continuous secondary outcomes will be analysed using a linear mixed effects regression model similar to the primary outcome. Dichotomous secondary outcomes will be assessed using a logistic regression model. A sensitivity analysis will be undertaken, adjusting for service characteristics that appear imbalanced between groups at baseline (if this is present). Additionally we will plan to undertake a subgroup analysis examining potential intervention effect among services with the lowest baseline outdoor free play opportunities (specified as the lowest third quartile).

For the primary outcome (mean minutes of opportunities for outdoor free play), a sample of 100 ECEC services will enable us to detect an absolute difference of 25.34 min/day in the time children have the opportunity to spend in outdoor environments during free play assuming a standard deviation of 43 min with 80% power and an alpha of 0.05 based on previous research [65]. An additional 27 min of outdoor free play time will increase total outdoor free play time to > 1 h for many services, resulting in an additional 10 min of MVPA [13]. An increase of 10 min in MVPA in children aged 3 to 6 years has been found to have clinically significant beneficial effects on fat mass and peak bone mass [66, 67].

For the secondary outcome (the proportion of services implementing the recommended indoor-outdoor free play routines per day for an entire week), a sample of 100 ECEC services (50 per group) will enable us to detect an absolute difference of 27.50%, assuming that 31% of control services implement an indoor-outdoor program as recommended, with 80% power and an alpha of 0.05 based on previous research [65].

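### The entry rule sets no minimum indoor-only time, and the primary model and subgroup use baseline outdoor minutes rather than the indoor-only minutes available to convert

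*Protocol article*

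**What the plan says.** All references are to the Protocol article.

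- **Entry (Eligibility).** Services must report "at least one session of indoor only free play across five consecutive days, where the opportunity for outdoor free play is not made available". No session length or total time is stated. Recruitment procedures places this check in a telephone call before consent.
- **Mechanism (Theoretical frameworks).** The text says that, primarily, "services are supported to modify their play routines to convert any indoor only free play routine to also incorporate outdoor play". Table 1 names the target behaviour as "Amending all indoor only free play time to allow children the opportunity to access outdoor areas".
- **Primary outcome (Abstract, Methods).** "mean minutes/day (calculated across 5 consecutive days) of outdoor free play opportunities".
- **Sample size (Analysis and sample size).** "a sample of 100 ECEC services will enable us to detect an absolute difference of 25.34 min/day", "assuming a standard deviation of 43 min with 80% power and an alpha of 0.05 based on previous research". Room to gain is not mentioned.
- **Primary model and subgroup (same section).** The fixed effects are group, the baseline value of the outcome (outdoor minutes), service size and region. The subgroup is the services with the lowest baseline outdoor free play. Stratification is by service type and size.
- **Where indoor-only time does appear (Secondary outcomes).** The Free Play Record (FPR) captures the duration of indoor-only play at baseline, 6 and 18 months. That time is part of the denominator of the secondary proportion, and the presence of any indoor-only session decides the dichotomous secondary outcome.

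**The concern.** If the strategy acts mainly by opening indoor-only sessions to the outdoors, a service's room to gain is roughly its baseline indoor-only time. Entry depends on a count of sessions, whereas the primary outcome is in minutes per day averaged over five days. A service that only just qualifies may have very little to convert.

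Two things are at stake. If many enrolled services are near the threshold, the average effect is diluted and the trial has less power than planned. The analysis of the primary outcome also has no term for room to gain. Baseline outdoor minutes do not supply one, because few outdoor minutes can reflect a short free-play day as well as a large block of indoor-only play.

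**Working it through.** **Inputs.** From Analysis and sample size: 100 services, SD 43 min, 80% power, alpha 0.05, difference 25.34 min/day. From Randomisation and blinding: 1:1 allocation, so 50 per arm. Two-sided testing is assumed. The documents do not give the length of an indoor-only session, so 30 to 90 min is assumed. They also do not give the distribution of baseline indoor-only minutes.

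**1. The plan's own figure.** Standard error of the difference = 43 × √(2/50) = 8.6. Detectable difference at 80% power = 8.6 × (1.960 + 0.842) = 24.09 min/day (24.33 with the t distribution). Power for 25.34 = Φ(25.34/8.6 − 1.960) = 83.8% (83.1% with t). The stated 25.34 is not reproduced exactly. The gap is on the cautious side and does not affect this point.

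**2. Ceiling on gain by conversion.** With total free play time fixed, ceiling (min/day) = indoor-only minutes over five days ÷ 5. A gain of 25.34 needs 25.34 × 5 = 126.7 indoor-only minutes over the five days. For a service with one session:

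| Assumed session length | Ceiling, min/day | Share of 25.34 |
|---|---|---|
| 30 min | 30/5 = 6 | 24% |
| 60 min | 60/5 = 12 | 47% |
| 90 min | 90/5 = 18 | 71% |

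A single session longer than about 127 min would reach 25.34.

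**3. Effect on power, by share of capped services.** Suppose a share f of services gain exactly their cap c, the rest gain 25.34, controls do not change and the SD stays at 43. Mean difference = f × c + (1 − f) × 25.34, and power = Φ(mean/8.6 − 1.960).

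| Cap c | f = 10% | f = 25% | f = 50% |
|---|---|---|---|
| 6 | mean 23.4, power 78% | 20.5, 66% | 15.7, 45% |
| 12 | 24.0, 80% | 22.0, 73% | 18.7, 58% |
| 18 | 24.6, 82% | 23.5, 78% | 21.7, 71% |

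For 80% power the mean must be at least 24.09, so f can be at most (25.34 − 24.094)/(25.34 − c). That is 1.246/19.34 = 6%, 1.246/13.34 = 9% and 1.246/7.34 = 17% for caps of 6, 12 and 18. These are scenarios. Nothing in the documents fixes f.

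**4. Why outdoor minutes are an imperfect proxy.** Indoor-only minutes = total free play minutes − minutes with outdoor access. Two services with the same outdoor minutes have different room to gain whenever their totals differ. Totals can be expected to differ, since Sampling frame describes preschools open 6 to 8 hours a day and long day care open 8 hours or more. Adjusting for, or subgrouping on, outdoor minutes alone leaves that difference out.

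**The case against.** The other side has a strong case, and much of it stands.

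- **The entry rule is coherent.** The dichotomous secondary outcome classes a service with any exclusively indoor free play as not implementing. The entry rule admits exactly those services, and broad entry suits a trial delivered at scale. This stands. A reader might infer that entry should require about 127 indoor-only minutes over five days. The documents do not support that: such a minimum would narrow the population for a scale-up question and would move screening from a telephone call to a five-day record.
- **25.34 min/day is a mean difference between arms.** It is not something each service must reach. This stands. Low-headroom services cost power only in proportion to their share, which is unknown.
- **The ceiling assumes fixed total free play.** The protocol says the strategy primarily converts, and its stated aim is more outdoor free play time. Longer outdoor sessions would also raise the outcome. This stands, so the ceilings apply to gain by conversion only.
- **Indoor-only minutes are used.** A reader might infer that the plan ignores them, or that a null result could not be read. Neither holds. If services had little to convert and converted it, the secondary proportion would approach 100% and more services would meet the full-day definition. If the strategy failed, neither would move. Fidelity is measured too.
- **Such detail may sit in an analysis plan that is not shown.** This is fair as far as it goes. However, the protocol itself lists the primary covariates and chooses the subgroup variable, and that choice can be assessed.

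What the objection does not remove is that the secondary outcomes describe conversion for each arm as a whole. They do not estimate how the effect on primary-outcome minutes varies with the minutes available to convert.

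**Conclusion.** The point holds in limited form. The entry rule has no minimum duration, so services with little indoor-only time can enter. For a service with one session of 30 to 90 min, conversion can yield at most 6 to 18 min/day, or 24% to 71% of the planned mean difference. This rests on the assumed session lengths and on fixed total free play time. The loss of power cannot be stated, because the share of such services is not given. In the scenarios above it runs from negligible to serious.

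Baseline indoor-only minutes are collected and feed the secondary outcomes, but they are absent from the primary model and the subgroup, where baseline outdoor minutes stand in imperfectly. This is an inexpensive opportunity missed in the analysis of the primary outcome. It does not show that the planned difference is out of reach or that the entry rule is wrong.

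**What to change.** 1. Keep the eligibility rule as it is.
2. Add baseline indoor-only free play minutes per day, taken from the baseline FPR, to the pre-specified covariates of the primary model, alongside the baseline outcome, service size and region.
3. Pre-specify a treatment-by-baseline-indoor-only-minutes interaction, with the covariate kept continuous, as an exploratory analysis beside the subgroup on low baseline outdoor minutes. Report it as an estimate with a confidence interval. The interaction is what addresses whether there was little to convert; the main-effect covariate alone can only add precision.
4. Do not report a per-service share of indoor-only minutes converted. That ratio is unstable when the baseline minutes are small, which is the case of interest here.

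The cost is one degree of freedom in the primary model and one extra exploratory analysis. No new data, visits or recruitment changes are needed. With 50 services per arm the interaction may be imprecise, so it should be used to interpret the primary result and not as a confirmatory test.
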